### Phase 2: sequential qualitative assessment

In phase 2 of the trial, the primary researcher will employ phenomenological methodology, to gather descriptions of resident and staff experiences of phase 1 of the trial.

#### Semistructured interviews with residents

The primary researcher will use a semistructured interview approach with the residents recruited into phase 2. The interviews will be organised around a topic guide, designed to explore the perspectives of the residents on taking part in research, and the experiences of residents within the care homes randomised to all three allocated interventions. The interviews will be conducted face-to-face, to provide a means of acquiring insight and understanding of the resident experience and values [42] and are anticipated to last for 30 to 60 min for each individual.

#### Staff focus groups

The primary researcher will facilitate a focus group discussion with between two and eight staff within each participating care home, for which management approval has been received for focus group participation. This technique has been chosen as a means of obtaining information about a range of staff experiences and to highlight any variations in perspectives between the staff within each home and between care home types [43]. The groups are anticipated to last 1–2 h for the duration. It is hoped that the focus groups will generate a lot of information in a relatively short amount of time. As the staff within a care home work closely together, it is anticipated that they will be able to engage in discussion.

In light of the possibility for digression, the interviews and focus groups will be audio taped, to enable transcription for analysis. Permission to audio tape the interviews and focus groups will be obtained prior to the start of the phase 2.

#### Sample size

No formal sample size calculation was performed for this trial, as the primary outcome measures are concerned with recruitment, retention and the feasibility and acceptability of the trial [44]. Any investigations of changes in key study parameters were exploratory only. Based on the capacity of the selected care homes (29–72) and the risk of malnutrition within the UK elderly care home population (30%–42%), it was estimated that between 9 and 30 residents would be identified as at risk of malnutrition within each participating care home and would be considered for receipt of the assigned nutritional intervention. It was decided that this estimated sample size of *n* = 50 to *n* = 180 would provide sufficient data to assess trial feasibility. Effective sample size calculation for the future definitive trial will be informed by rates of recruitment and retention.

#### Cluster randomisation

Cluster randomisation took place following recruitment and baseline assessment within each care home, via the University of Birmingham Clinical Trials Unit randomisation service. Each care home was randomised using a computer-generated random number list to dietetic-led food-based intervention, dietetic-led ONS intervention or the standard care home nutritional intervention for malnutrition. Stratification by care home type ensured that one nursing home and one residential home was allocated to each intervention arm. The primary researcher communicated confirmation of the intervention allocation and the care home trial number to each participating care home.

#### Statistical methods

The Birmingham Clinical Trials Unit (BCTU) will provide support with the analysis of data. Statistical analyses will be performed using IBM SPSS, version 21.

### Phase 1 quantitative analysis

#### Descriptive statistics

As effective hypothesis testing requires a powered sample size [44], analysis will be limited to descriptive statistics and an exploratory analysis to provide estimates of key parameters and to inform the definitive trial design.

Baseline variables, as well as data on resident withdrawals, mortality, healthcare resource-usage, adverse events and compliance collected throughout the trial, will be summarised as *n* (%), mean (standard deviation) or median (interquartile range), as appropriate, to characterise the overall sample and to highlight any imbalances between the randomised trial arms. A standard CONSORT diagram (Figure 2) will be used to describe the flow of residents through the trial. This information will summarise the feasible eligibility, recruitment and 3- and 6-month follow-up rates. Potential differences in attrition rates and other data quality issues will be identified and used to inform the design of the definitive trial.

#### Statistical analyses

The detailed statistical approach will be published subsequently with the results of the trial.

All continuous data will be tested for normality using Kolmogorov-Smirnov. Categorical variables will be compared between intervention arms at baseline using the chi-square test. Mean changes in continuous outcome measures, such as nutrient intake and anthropometric parameters, will be calculated at 3 and 6 months, along with 95% confidence intervals. Group mean changes will be compared between each of the dietetic-led intervention arms and the standard care arm, using the independent-sample *t*-test for normally distributed data and the Mann-Whitney *U* test for data, which violates normality. Where sensitivity to change is suggested from the 95% confidence interval, the independent-sample *t*-test will be used to compare food-based intervention with ONS intervention for that particular outcome measure.

Completion rates and missing data will be summarised for all outcome assessments, along with estimates and variances, to determine the most appropriate primary outcome measure for a definitive trial. If an appropriate primary outcome measure is identified within this trial, the data collected will help to inform the calculation of the intracluster correlation coefficient (ICC), the design effect (DE) and the effective sample size for a definitive trial.

where *(m × k)* is the total number of subjects in a clustered trial, *m* is the number of subjects in a cluster and *k* is the total number of clusters.

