The trial will have a number of quantitative objectives:To assess how many care homes for the elderly accept the invitation to participate in a nutritional intervention feasibility trialTo determine whether the eligibility criteria for malnourished care home residents are too open or too restrictive, by estimating feasible eligibility and recruitment rateTo assess retention of care homes and residents, by estimating 3- and 6-month follow-up ratesTo investigate the acceptability of nutrition support interventions to malnourished care home residents, in terms of compliance, and to care home staff in terms of adherence to the intervention scheduleTo determine the acceptability and feasibility (and factors influencing this) of the different outcome measures as methods to measure efficacy of nutritional interventions within a definitive trialTo investigate the completion and accuracy of nutritional screening and questionnaire completion by care home staffTo determine how many malnourished care home residents are able to participate in PROMs and to complete the questionnairesTo measure key outcome domains (for completion rates, missing data, estimates, variances and 95% confidence intervals for the difference between the intervention arms) for malnourished care home residents including physical outcome measures and PROMsTo collect and synthesise data, from which to estimate the intracluster correlation coefficient (ICC) and inform the sample size of a definitive trial

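### The baseline chi-square tests should be dropped, and the planned tests of group change fit poorly with a trial that the protocol says is too small for effective hypothesis testing

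*Protocol article*

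**What the plan says.** The Descriptive statistics section sets the scope: "As effective hypothesis testing requires a powered sample size [44], analysis will be limited to descriptive statistics and an exploratory analysis". The exploratory part is there to supply estimates and inform the definitive trial. The same section has baseline variables summarised by arm "to highlight any imbalances between the randomised trial arms". The Sample size section reports no formal calculation and calls investigations of change exploratory.

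The Statistical analyses section then names three sets of tests:
- At baseline, "Categorical variables will be compared between intervention arms at baseline using the chi-square test".
- For outcomes, "Group mean changes will be compared between each of the dietetic-led intervention arms and the standard care arm", by independent-sample t-test or Mann-Whitney test. Mean changes are also to be given with 95% confidence intervals.
- A t-test of food-based intervention against oral nutritional supplements (ONS), to be done "Where sensitivity to change is suggested from the 95% confidence interval".

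Among the objectives in Aims and objectives are completion rates, missing data, estimates, "variances and 95% confidence intervals for the difference between the intervention arms". No objective there asks for a test.

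**The concern.** Lack of power is the protocol's own reason for holding back from hypothesis testing, yet it then specifies tests. The two sections need to be reconciled.

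The baseline tests are the weaker part of the plan. Screening and consent came before randomisation (Individual consent for PROM's), and homes were randomised after recruitment and baseline assessment (Cluster randomisation). Any baseline difference between arms is therefore due to chance. A p-value cannot tell the reader whether an imbalance is large enough to matter, which is what the descriptive table is for.

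For the outcomes, an exploratory p-value from a small trial with two homes per arm is unreliable in both directions. A useful difference may fail to reach significance, and a difference between homes may look like an effect of the intervention.

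**Working it through.** **Inputs from the protocol.** Expected total n = 50 to 180 (Sample size); three arms with one nursing and one residential home each (Cluster randomisation); resident retention criterion of 65% or more (Aims and objectives).

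**Assumptions, not in the protocol.** Equal arms, two-sided alpha 0.05, the effect sizes shown, and an intracluster correlation (ICC) of 0.02 to 0.10.

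**The protocol's own size figure.** Per home, 29 × 0.30 = 8.7 (stated 9) and 72 × 0.42 = 30.2 (stated 30). In total, 6 × 30 = 180, as stated. The lower total is 6 × 9 = 54 against the stated 50, apparently rounded down, which does not affect this point. Each arm then has 50/3 ≈ 17 to 180/3 = 60 residents in two homes, or about 8 to 30 per home.

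**Baseline: a sizeable imbalance can be non-significant.** Take 6, 8 and 11 of 17 (35%, 47%, 65%), an illustrative pattern. Expected counts are 25/3 = 8.33 with and 26/3 = 8.67 without the characteristic in each arm. The squared deviations sum to 2.33² + 0.33² + 2.67² = 12.67. Chi-square = 12.67/8.33 + 12.67/8.67 = 2.98 on 2 df, p = 0.23. Expected counts fall below 5 for any characteristic with prevalence under 5/17 = 29% at 17 per arm, or under 5/60 = 8% at 60 per arm.

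**Baseline: clustering pushes the other way.** The variance of an arm's proportion is inflated by the design effect, DE = 1 + (m − 1) × ICC, with m residents per home. The Pearson statistic is inflated by about the same factor, so on 2 df the chance of passing the 5% point (5.99) under the null is about exp(−5.99/(2 × DE)):
- m = 8: DE = 1.14 to 1.70, giving 7% to 17%.
- m = 30: DE = 1.58 to 3.90, giving 15% to 46%.

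**Outcomes: power of a two-sample t-test, ignoring clustering, at 65% retention**

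| Total n | Per arm | 0.5 SD | 0.8 SD |
|---|---|---|---|
| 50 | 50/3 × 0.65 = 10.8 | 20% | 43% |
| 180 | 60 × 0.65 = 39 | 59% | 94% |

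A normal approximation gives 21% and 60% for 0.5 SD.

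**Outcomes: false-positive rate of the unadjusted t-test** (simulation with two homes per arm, 20,000 runs)

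| Residents per home | ICC 0.02 | ICC 0.05 | ICC 0.10 |
|---|---|---|---|
| 8 | 6.7% | 9.3% | 13.9% |
| 30 | 11.9% | 21.2% | 32.8% |

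These rates are for full retention. At 65% retention, the approximation 2 × (1 − Φ(1.96/√DE)) gives 6% to 10% at n = 50 and 9% to 25% at n = 180. The simulation did not model the stratification by home type. To the extent that type explains differences between homes, the inflation would be smaller.

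**Width of an interval that allows for clustering.** A comparison of home means (two against two, 2 df, t = 4.30) has a 95% half-width of 4.30 × √(ICC + (1 − ICC)/m) SD. At ICC 0.05 this is 4.30 × √(0.05 + 0.95/8) = 1.77 SD for m = 8, and 4.30 × √(0.05 + 0.95/30) = 1.23 SD for m = 30. Ignoring clustering, 1.96 × √(2/n) gives 0.68 SD (n = 50/3 per arm) and 0.36 SD (n = 60 per arm).

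**The case against.** The strongest reply is that there is no flat contradiction. The sentence that limits the analysis allows an exploratory analysis as well as description, and the Sample size section already labels analyses of change exploratory. This stands for the outcome comparisons: they fit poorly with the stated purpose, but they are not forbidden by it. It does not rescue the baseline tests, which estimate nothing and repeat a check that the descriptive table makes.

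A reader might go further and infer that non-significant results will be taken as balance or as no effect, and so discredit an intervention or a measure. The document does not support this. It gives no significance threshold for the tests and no rule for reading a null result. It plans confidence intervals, and the food-based against ONS comparison depends on an interval rather than a p-value. None of the success criteria uses a p-value, and the future primary outcome is to be chosen from completion rates, missing data, estimates and variances.

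Nor can one say that a worthwhile effect would usually be non-significant. That describes the low end of the expected size; at n = 180, unadjusted power for 0.8 SD is 94% even at 65% retention.

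It is also fair to say that a t-based 95% interval excludes zero exactly when p < 0.05. Replacing the test by its own interval would therefore keep the clustering error, and the fix has to deal with that.

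Finally, the article defers the detailed statistical approach to the results paper. That can cover how p-values are presented, but the tests themselves are already named.

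**Conclusion.** The point holds as a mismatch between purpose and method, with one clear error. The baseline chi-square tests examine a null that randomisation after baseline assessment makes true, duplicate the descriptive check, and ignore clustering. They can pass over a sizeable imbalance in the smallest expected trial and flag chance differences between homes in a larger one.

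The outcome tests answer no stated objective, and their p-values are unreliable both ways: power for 0.5 SD of about 20% to 60%, and false-positive rates of about 7% to 33%. These figures rest on the assumed alpha, effect size, equal arms and ICC. The power figures also ignore clustering and are taken at 65% retention, whereas the false-positive rates are at full retention. Misreading is a risk that the wording leaves open, not something the protocol prescribes.

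**What to change.** 1. Delete the baseline chi-square tests. Tabulate baseline variables by arm and by home, and judge any imbalance by its size and its relevance to the outcome.
2. Replace the tests of group change, including the food-based against ONS t-test, with between-arm differences and 95% confidence intervals that allow for clustering by home, labelled exploratory.
3. If any test is kept, state that its p-value will not be used to judge balance or efficacy.

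The cost is a change of analysis wording; no new data are needed. The results paper would carry no p-values. With two homes per arm, the intervals would be wide and imprecise, which describes fairly what the trial can show about differences between arms.

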### Setting and population

The feasibility trial is being conducted within the borough of Solihull, West Midlands, in England. Prior to trial commencement, 17 care homes in Solihull, providing accommodation for older people, were receiving regular dietetic input, to improve the identification and first-line nutritional management of malnutrition. Six privately owned care homes were invited to take part in the trial. The care homes were purposively sampled to obtain a diverse sample based on ownership, size and type of care provided (nursing and/or residential), to enable the evaluation of feasibility and acceptability of the trial design and methodologies across a range of long-term care settings.

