### Data collection and outcome assessments

#### Timing of assessments

Assessments were made at baseline, at 3 months and at 6 months (Table 2). All assessments were conducted within the care homes.

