*Healthcare resource usage*	*Care staff measured*	The healthcare resource usage questionnaire to be piloted within this trial has been developed from consideration of existing instruments submitted for use in residential care settings on the ‘MRC Database of Instruments for Resource Use Measurement’ (DIRUM). The questionnaire will be completed by care home staff, from baseline to 3 months and from 3 to 6 months for each participating resident.
*Health state using The EuroQol-5D (EQ-5D)*	*Participant rated*	There is no malnutrition-specific measure of health state or quality of life for patients, so these well-established and validated measures will be piloted within this population to inform as to whether they are appropriate for completion by care home residents with varying cognitive function. The Euroqol group and the Dartmouth CO-OP project have granted permission to use the tools
*Quality of life using the CO-OP Quality of life chart*	*Participant rated*	
*Visual analogue scale (VAS) for self-perceived appetite and dietary satisfaction*	*Participant rated*	A VAS tool has been developed to measure the following subjective sensations; ‘hunger’, ‘appetite’, ‘dietary satisfaction’, ‘pleasantness of meals’, ‘pleasantness of snacks’ and ‘pleasantness of drinks’ and will be piloted within this trial.

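### Arms are compared on change scores without baseline adjustment, which costs precision and leaves the exploratory estimates exposed to chance baseline imbalance between arms of two homes

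*Protocol article*

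**What the plan says.** The Statistical analyses section states that "Mean changes in continuous outcome measures, such as nutrient intake and anthropometric parameters, will be calculated at 3 and 6 months". Intervals at the 95% level are to accompany them. The next sentence fixes the comparison: "Group mean changes will be compared between each of the dietetic-led intervention arms and the standard care arm, using the independent-sample". The test meant is the two-sample t-test, replaced by Mann-Whitney U where normality fails. No baseline covariate is named. The Descriptive statistics section proposes to show imbalances between arms but not to adjust for them.

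Baseline values exist. Under Timing of assessments: "Assessments were made at baseline, at 3 months and at 6 months". Table 2 ticks baseline for every measure. One measure has no clear pre-intervention value: Table 3 describes healthcare resource use "from baseline to 3 months and from 3 to 6 months for each participating resident".

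The Cluster randomisation section places randomisation after recruitment and baseline assessment. Stratification by home type gives each of the three arms one nursing and one residential home. Under Setting and population, the six homes were "purposively sampled to obtain a diverse sample based on ownership, size and type of care provided".

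**The concern.** Baseline values taken before allocation are valid covariates and are already in hand. A plain change score uses them inefficiently, because it subtracts the whole baseline value when only a fraction r of it carries forward. Two things follow. The estimate is noisier than it needs to be, and an arm that happens to start higher will appear to change less even if treatment does nothing.

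This matters because the numbers are outputs of the trial. The quantitative objectives ask for variances and confidence intervals for arm differences on the key outcomes. The Statistical analyses section uses the estimates and variances to choose a primary outcome for the definitive trial and to inform its sample size. The penalty depends on r, so change scores put outcomes with low baseline/follow-up correlation at a disadvantage against highly correlated ones. If the definitive trial were analysed with baseline adjustment, change-score SDs would also overstate its resident-level variance.

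**Working it through.** **Inputs from the protocol.** Three arms with two homes each (Cluster randomisation). Home capacity 29 to 72 and malnutrition risk 30% to 42% (Sample size). The protocol gives no SD, ICC or baseline/follow-up correlation, so r and the ICC below are assumptions, shown over a range.

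**The plan's own figure.** 29 × 0.30 = 8.7 and 72 × 0.42 = 30.24, which reproduces the stated 9 to 30 at-risk residents per home. These serve as cluster size m.

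**1. Precision.** With equal variances σ² at both times and independent residents, the change-score variance is 2(1−r)σ² and the baseline-adjusted residual variance is (1−r²)σ². The ratio of adjusted to change-score variance is (1−r²)/[2(1−r)] = (1+r)/2.

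| r | Adjusted / change-score variance | Reduction |
|---|---|---|
| 0.3 | 0.65 | 35% |
| 0.5 | 0.75 | 25% |
| 0.7 | 0.85 | 15% |
| 0.9 | 0.95 | 5% |
| 0.95 | 0.975 | 2.5% |

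**2. How likely is imbalance?** The difference in baseline means between two arms of two homes has SD √{2[ICC/2 + (1−ICC)/(2m)]} = √{ICC + (1−ICC)/m}, in outcome SDs. At ICC 0.10:
- m = 9: √(0.10 + 0.90/9) = 0.447, so P(|difference| > 0.25 SD) = 0.58.
- m = 30: √(0.10 + 0.90/30) = 0.361, so P = 0.49.

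Over ICC 0 to 0.20 and m = 9 to 30, the SD runs from 0.18 to 0.54 and the probability from 0.17 to 0.64.

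**3. Shift given an imbalance.** If one arm starts higher by d, its change-score contrast moves by −(1−r)d. For d = 0.30 SD this is −0.15 SD at r = 0.5, −0.09 at r = 0.7 and −0.015 at r = 0.95. As an illustration in kcal, take an assumed imbalance of 200 kcal/day. The shift is then 0.5 × 200 = 100 kcal at r = 0.5 (one sixth of the 600 kcal target), 60 at r = 0.7 and 10 at r = 0.95.

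**4. Simulation with homes included.** No treatment effect, two homes per arm, ICC 0.10, m = 9 or 19, 4,000 runs per setting.
- Over all randomisations, mean estimates lay between −0.008 and +0.005 SD for both methods.
- The next results are for runs where the arm started more than 0.25 SD higher. With r = 0.5 for residents and for homes, the change score averaged −0.27 to −0.24 SD and resident-level adjustment −0.01 to 0.00.
- In the same runs, with r = 0.5 for residents but 0.9 for homes, the change score averaged −0.17 to −0.10 and adjustment +0.09 to +0.14.
- The variance ratio of the estimates (adjusted to change score) over all runs was (0.395/0.451)² = 0.77 at m = 9 and (0.334/0.386)² = 0.75 at m = 19 when the two correlations were both 0.5. With home correlation 0.9 it was (0.336/0.345)² = 0.95 and (0.267/0.258)² = 1.07.

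**The case against.** A reader might infer that the change-score comparison is biased outright, or that selecting residents on MUST produces a spurious arm difference through regression to the mean. The documents support neither. Allocation was random and followed baseline assessment, so the contrast is unbiased in expectation, as the simulation shows. The same MUST rule applies in every home, so regression from selection cancels between arms on average. It stays in each arm's own mean change.

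Other points against the concern also stand in part:
- Type of care, one of the three features on which homes were chosen to differ, is balanced by stratification. Ownership, size and case mix are left to chance.
- For outcomes that barely move between visits, perhaps weight and BMI, the gain is trivial.
- Adjustment is not a full cure. Where home differences persist more than resident differences, resident-level adjustment can err in the opposite direction, and its precision gain can disappear.
- The comparisons are declared exploratory, and no success criterion rests on an arm difference. No primary outcome or analysis model has yet been fixed for the definitive trial.

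The protocol also defers the detailed statistical approach to the results publication. That does not remove the point, because the tests are already named and they use unadjusted changes.

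**Conclusion.** The point holds as avoidable loss of precision and exposure to chance imbalance in an exploratory analysis. With independent residents and equal variances, adjustment would cut residual variance by about 25% at r = 0.5 and by 2.5% to 5% at r = 0.95 to 0.9. A baseline imbalance above 0.25 SD is about an even chance at ICC 0.10, and (1−r) of any imbalance passes into the estimate. These sizes rest on assumed values of r and the ICC. The precision gain also depends on how far home-level differences persist. The point concerns continuous outcomes with a baseline value, so resource use falls outside it. The consequence is for the estimates and variances handed to the definitive trial; no conclusion on effectiveness is affected.

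**What to change.** Replace the change-score tests for each continuous outcome that has a baseline value. Estimate the 3- and 6-month arm difference with the resident's baseline value as a covariate, in an analysis that accounts for home. Report:
- the adjusted difference with its 95% confidence interval;
- the adjusted SD;
- the baseline/follow-up correlation, so that the definitive trial can be sized for whichever model it uses.

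Keep mean change by arm as a descriptive summary. Label the arm differences exploratory, and state that with four homes per contrast, adjustment may not fully remove a home-level imbalance.

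No new data are needed. The cost is in analysis wording and in candour about precision: a home-level comparison of two arms has only 4 − 2 = 2 degrees of freedom, so intervals that respect clustering will be wide.

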**Methods:**

Trial recruitment began in September 2013 and concluded in December 2013. Six privately run care homes in Solihull, England, were selected to establish feasibility within different care home types. Residents with or at risk of malnutrition with no existing dietetic intervention in place were considered for receipt of the allocated intervention. Randomisation took place at the care home level, using a computer-generated random number list to allocate each home to either a dietetic intervention arm (food-based or prescribed supplements) or the standard care arm, continued for 6 months. Dietetic intervention aimed to increase daily calorie intake by 600 kcal and protein by 20–25 g.

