## Trial status

A prospective cluster randomised feasibility trial with 6-month intervention. A sequential, explanatory mixed method design was proposed, beginning with a quantitative method to assess trial feasibility (phase 1), followed by a qualitative method, involving detailed exploration with a few individuals [33] (phase 2).

A cluster trial design has been chosen primarily to avoid contamination [34], because the assigned care staff receiving additional training and support cannot be expected to treat individual residents differently, but it is also being used for practical reasons. The aim of the trial is to assess the feasibility and acceptability of delivering and evaluating nutritional interventions for malnutrition in the care home setting, and hence the home is the unit of randomisation.

### Phase 1

Recruitment for phase 1 of the trial began in September 2013 and concluded in December 2013. The quantitative phase follows a controlled experimental design, collecting data on changes in anthropometric markers and nutrient intake along with the use of quantitative questionnaires. The trial needed to be open label due to the nature of the nutritional interventions under investigation.

### Phase 2

Recruitment for phase 1 of the trial began in July 2014 and is expected to conclude in October 2014. Following phase 1, the quantitative findings will be further explored with a sample of residents and care home staff, using semistructured interview and focus group techniques. The qualitative findings will be used to complement, explore and explain the quantitative data collection and will ensure that resident and staff perspectives are used to inform the future trial design.

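### Homes are randomised, two per arm, but arms are compared with resident-level tests that ignore home, so between-arm p-values and 95% intervals are expected to be too small and too narrow when outcomes correlate within homes

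*Protocol article*

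**What the plan says.** Allocation is by home. The abstract says "Randomisation took place at the care home level", and the Trial status section, after arguing that shared staff cannot treat residents differently, concludes "hence the home is the unit of randomisation". The Setting section reports that "Six privately owned care homes were invited to take part in the trial". The Cluster randomisation section adds: "Stratification by care home type ensured that one nursing home and one residential home was allocated to each intervention arm". That makes two homes in each of three arms.

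The Statistical analyses section fixes the comparison: "Group mean changes will be compared between each of the dietetic-led intervention arms and the standard care arm", by independent-sample t-test, or by Mann-Whitney U test where normality fails. Where a 95% confidence interval suggests sensitivity to change, a further t-test compares food-based intervention with ONS. For baseline data, "Categorical variables will be compared between intervention arms at baseline using the chi-square test". The quantitative objectives also promise 95% confidence intervals for the difference between arms.

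No home-level summary, random effect, robust standard error or design-effect correction is named for these comparisons. The ICC and design effect appear in the same section, but only as inputs to the definitive trial. The Descriptive statistics section, just before, says that "analysis will be limited to descriptive statistics and an exploratory analysis", because effective hypothesis testing needs a powered sample.

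**The concern.** The t, Mann-Whitney and chi-square tests take their standard error from variation between residents and treat each resident as a separate unit of evidence. Here the evidence about an intervention comes from two homes set against two homes. If homes differ in catering, staffing or case mix, residents of one home resemble each other. The resident-level standard error then leaves out part of the real uncertainty, and an ordinary difference between two pairs of homes can look like an intervention effect. The protocol's own reason for using clusters, shared staff, makes such correlation plausible.

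At stake are the between-arm estimates that the trial is meant to hand on with valid uncertainty, and the possible use of an interval to decide whether food-based intervention is tested against ONS. There is also a tension in the text: one section limits the analysis to description and exploration, and the next prescribes hypothesis tests, including baseline tests.

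**Working it through.** **Cluster size, from the Sample size section.** Capacity is 29 to 72 places and malnutrition risk 30% to 42%. 29 × 0.30 = 8.7, or 9; 72 × 0.42 = 30.2, or 30. The stated 9 to 30 per home is reproduced. The upper total is 6 × 30 = 180, as stated. The lower is 6 × 9 = 54 against a stated 50, which looks like rounding and does not matter here. The recruitment target of at least 50 gives 50 / 6 = 8.3 per home, so m = 8 to 30 is used below.

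**ICC.** None is given. Assumed range: 0.01 to 0.10.

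**Design effect with no home-type effect.** DE = 1 + (m − 1) × ICC.
- m = 8: 1.07 at ICC 0.01, 1.35 at 0.05, 1.70 at 0.10.
- m = 30: 1.29, 2.45, 3.90.

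The true standard error is √DE times the planned one: √1.07 = 1.03 at the low end and √3.90 = 1.97 at the high end. Effective residents per arm (2m / DE) fall from 16 to 16 / 1.70 = 9.4 at m = 8, ICC 0.10, and from 60 to 60 / 3.90 = 15.4 at m = 30, ICC 0.10.

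**Type I error of the planned t-test.** I simulated 40,000 null trials per setting: two homes against two, one of each type per arm, normal data, pooled t-test at 5%. The last three columns vary how much of the between-home variance is due to home type, which the stratification balances across arms.

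| m | ICC | none | half | all |
|---|---|---|---|---|
| 8 | 0.01 | 5.9% | 5.4% | 5.0% |
| 8 | 0.05 | 9.2% | 6.5% | 4.3% |
| 8 | 0.10 | 13.6% | 8.9% | 3.8% |
| 20 | 0.01 | 7.3% | 6.1% | 4.9% |
| 20 | 0.05 | 16.5% | 10.3% | 4.3% |
| 20 | 0.10 | 25.8% | 15.5% | 4.0% |
| 30 | 0.01 | 8.5% | 6.6% | 4.7% |
| 30 | 0.05 | 21.4% | 13.3% | 4.4% |
| 30 | 0.10 | 33.0% | 21.0% | 3.7% |

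**Width of a home-level interval.** With between-home variance pooled over six homes in three arms, df = 6 − 3 = 3 and the critical t is 3.18. Fitting home type as well leaves 6 − 3 − 1 = 2 df and a critical t of 4.30. The planned test uses 4m − 2 df: critical t 2.04 at m = 8 and 1.98 at m = 30. With no home-type effect, the ratio of the home-level to the planned half-width is √DE × (home-level t) / (planned t).
- 3 df: 1.03 × 3.18 / 2.04 = 1.6 (m = 8, ICC 0.01), up to 1.97 × 3.18 / 1.98 = 3.2 (m = 30, ICC 0.10).
- 2 df: 1.03 × 4.30 / 2.04 = 2.2, up to 1.97 × 4.30 / 1.98 = 4.3.

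**The case against.** The strongest reply is that nothing important hangs on these tests. The primary outcomes are feasibility and acceptability, and no success criterion in the Aims and objectives section uses a between-arm comparison. The Sample size section calls changes in study parameters exploratory, a trials unit supports the analysis, and the detailed approach is to be published with the results. This stands as a limit on the consequences. It does not rescue the method: the section names specific tests that ignore the unit of randomisation, and an exploratory interval still has to reflect the uncertainty it claims to show.

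The second reply also stands in part. Stratification balances home type across arms, so the inflation is smaller when type explains part of the between-home variance. If it explains all of it, the t-test is slightly conservative.

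Two stronger readings are tempting, and the document supports neither.
- A reader might infer that every interval is too narrow and every p-value too small. That depends on the residual correlation within homes. Even when there is some, the planned interval in a single trial will not always be narrower than the home-level one.
- A reader might infer that the error decides the primary outcome of the definitive trial. The interval gates only the food-based versus ONS comparison. The primary outcome is to be chosen from completion rates, missing data, estimates and variances. Nor does the text say whether the trigger is the interval for a mean change or for a difference between arms.

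The conflict between the two analysis sections is likewise a tension rather than a flat contradiction, since exploratory analysis is expressly allowed.

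**Conclusion.** The point holds as a statement about expected behaviour. The named between-arm tests do not match the unit of randomisation, and their p-values and intervals are expected to be too small and too narrow whenever outcomes are correlated within homes beyond what home type explains. Over the assumed ICC range and 8 to 30 residents per home, the true type I error of the 5% t-test is about 6% to 33% with no home-type effect, and about 5% to 21% with half of the between-home variance due to type. The ICC range, the half share and normal data are assumptions. The figures are for the t-test; the Mann-Whitney and chi-square tests rest on the same independence assumption but were not simulated. The feasibility conclusions are untouched. What is affected is the between-arm estimation and, possibly, the step to comparing food-based intervention with ONS.

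**What to change.** In the Statistical analyses section:

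- Replace the resident-level between-arm tests with arm differences and 95% confidence intervals from home-level means. Pool the between-home variance over all six homes (3 df), or fit home type as a stratum (2 df), and say in advance which. With two homes per arm and equal weights, the standard error of a difference is √(s²/2 + s²/2) = s, where s is the pooled between-home standard deviation.
- Show each home's result beside the arm summary.
- Do not report resident-level between-arm p-values, including the baseline chi-square tests. Describe baseline balance by arm and by home. This also brings the section into line with Descriptive statistics.
- Do not let an unadjusted interval trigger the food-based versus ONS comparison. Report that difference in the same home-level form.

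A mixed model with a random home effect is not a good first choice, because two homes per arm give little information on the between-home variance.

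The cost is some rewording, a little extra analysis and wider intervals: about 1.6 to 3.2 times the planned width on 3 df, or 2.2 to 4.3 times on 2 df, under the assumptions above with no home-type effect. No further data are needed.
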